#### Medication adherence

We measure study participants’ self-reported medication adherence using the MARS-5, a self-assessment questionnaire with five items on a five-point scale that has previously been translated into Swedish.^36 37^

#### Quality of life and health economics

Quality of life is reported through a Swedish translation of the EQ-5D questionnaire, a standardised instrument consisting of two different components.^38^ In the first part, the respondents describe their health status in five different dimensions: walking ability, self-care, usual activities, pain/discomfort and anxiety/depressive symptoms. This part is followed by a visual analogue scale on which the respondents evaluate their own health status on a scale of 0–100.

#### Baseline characteristics

Baseline data include various personal characteristics, such as age, sex, living conditions in terms of cohabitation and home healthcare, diagnoses and current list of medications.

#### Sustained use and system-wide implementation

In addition to quantitative data, there will also be a qualitative component of the study. In order to capture the functionalities of the model, healthcare staff and participants involved in the intervention, and in some cases their next of kin, will be interviewed. An interview guide will be used and the questions will mainly focus on what does and does not work, overall satisfaction and personal experiences.^39^ The interview guide will also provide the opportunity to ask additional questions and elaborate on other issues. Moreover, the interviews will explore potential improvements, refinements to support ‘non-adopters’ and future implementation, as well as the opportunity to offer other comments and suggestions. The interviews will be audio recorded and transcribed verbatim, and the analysis will be conducted in a systematic process for developing codes and themes in interview data. While coding entails the work of naming the different categories, the thematisation process involves moving from so-called free-floating codes into an integrated framework of empirical themes.^40^

### Discontinuations and deviations from the protocol

An enrolled study participant can at any time withdraw consent to participate in the study or simply request that remaining phone calls be cancelled. Furthermore, the intervention can be discontinued for a number of other reasons, such as a change of living circumstances from home to residential care or repeated unanswered phonecalls. Importantly, we do not continue to record any new information from participants who withdraw their consent to participate in the study. Any documented death or withdrawn consent is censored in the survival analysis from that point and onwards. In all other cases of discontinued interventions, we collect data regarding hospital readmissions and emergency department visits for the complete 180-day period. Outcomes will primarily be analysed according to an intention-to-treat principle that includes all randomised participants for the time they were under observation. For outcomes other than time to event, we will apply the last observation carried forward in cases of missing data. Finally, there will be a supplementary per-protocol analysis of drug-related readmissions and questionnaires among participants who have received all prescheduled interviews during the follow-up period.

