The clinical pharmacist is one of many professions involved in preventing and managing DRPs. In principle, clinical pharmacy can be described as the science and practice of rational medication use and includes both medication reviews and counselling with patients as well as other healthcare professionals.^19^ Medication reviews conducted by clinical pharmacists have demonstrated a positive overall effect on both the appropriateness and cost of medication.^20 21^ Regarding the effect on hospital readmissions and other clinical outcomes, review data are less consistent and incorporate few randomised controlled trials (RCTs)^22–24^; however, there are relatively recent findings indicating that medication reviews conducted by clinical pharmacists on the ward can reduce drug-related readmissions to hospital in various groups of elderly people.^25–27^ Postdischarge interventions involving phone-based follow-ups by clinical pharmacists have reduced all-cause readmission rates, but these trials did not specifically target an elderly population.^28 29^ In addition, there seems to be a need for more RCTs that target medication discrepancies and errors during care transitions between hospital and primary care.^30^ In summary, there is still insufficient evidence for an optimal postdischarge intervention model that incorporates adherence elements and specifically addresses transitions of care involving elderly people.

In the present study, our primary aim is to investigate the effect of clinical pharmacists in transitional care on unplanned drug-related readmissions among people ≥75 years of age in a context where medication reviews conducted by clinical pharmacists within the hospital are already common practice. Our primary objective is to assess if intervention by a clinical pharmacist during a transition of care can reduce the risk of unplanned drug-related hospital readmission for 180 days after the person leaves the hospital. As secondary objectives, we will study the effects of the intervention on unplanned drug-related readmissions within 30 days, unplanned hospital visits (all-cause readmissions and emergency department visits), mortality, medication adherence and quality of life. Subgroup analyses will be based on the occurrence of heart failure and cognitive impairment. Moreover, we will collect qualitative interview data regarding the intervention.

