#### Hospital readmissions

The primary outcome is time until unplanned drug-related readmission within 180 days of being discharged from the hospital. As a secondary outcome, we also study these events within a narrower time frame of 30 days. The cause of each readmission will be retrospectively determined by a group of blinded physicians and pharmacists who are not otherwise involved in the study. This assessment group will reach a consensus decision regarding the causality of each readmission according to criteria from WHO, a method that has been used previously in similar studies.^25 34 35^ Readmissions classified as certain, probable or possible in this assessment will be regarded as drug related in the following statistical analysis. We also measure time until unplanned hospital visit (all-cause readmissions and emergency department visits), time until death, as well as frequencies of unplanned drug-related hospital readmissions and unplanned hospital visits.

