### Statistics

For a relative risk reduction of 40% in drug-related hospital readmissions from 19% to 11%, a total study population of 700 individuals is required to achieve a statistical power of 80% at our prespecified significance level of 0.05 for two-sided tests. The estimated incidence of drug-related readmissions was observed in a previous trial within the same community, although that study was limited to elderly people with major NCD.^25^

We will present time-to-event data in Kaplan-Meier survival curves and analyse differences in survival data between the groups through log rank tests and Cox proportional hazard models. Further investigations of subgroup effects and adjustments of the regression models will be based on heart failure and cognitive impairment as prognostic factors. We will analyse secondary outcomes using various appropriate statistical tests, such as X^2^ and independent sample t-test, depending on the type of variable.

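### Censoring deaths and plotting Kaplan-Meier curves modestly overstates each arm's 180-day probability of drug-related readmission; the primary test and the sample size are not affected

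*Protocol article*

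**What the plan says.** All references are to the protocol article.

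- *Hospital readmissions* defines the endpoint: "The primary outcome is time until unplanned drug-related readmission within 180 days of being discharged from the hospital". Death is not part of it. Time until death is a separate secondary outcome, and time until unplanned hospital visit is another.
- *Discontinuations and deviations from the protocol* sets the censoring rule: "Any documented death or withdrawn consent is censored in the survival analysis from that point and onwards".
- *Statistics* fixes the display and the test: "We will present time-to-event data in Kaplan-Meier survival curves and analyse differences in survival data between the groups through log rank tests", together with Cox models.
- The *Introduction* words the primary objective as finding out whether the intervention can "reduce the risk of unplanned drug-related hospital readmission for 180 days after the person leaves the hospital".

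Neither a cumulative incidence function nor death as a competing event is mentioned anywhere in the article. *Current trial status* lists 5 deaths as reasons for discontinuation among 161 randomised by November 2019.

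**The concern.** Withdrawal and death are different kinds of incomplete follow-up. After withdrawal a readmission may still happen and is merely unseen. After death it cannot happen. When deaths are censored, the Kaplan-Meier estimator treats the dead as if they carried the same future readmission risk as those still being followed. Its complement is then at best the risk in a hypothetical population without death, not the share of discharged patients who come back with a drug-related problem.

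The participants are 75 or older and have just had an emergency admission, so deaths within 180 days will occur. What is at stake is any absolute figure read from the curves: the probability in each arm, the difference between arms, and a number needed to treat (NNT) derived from that difference.

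**Working it through.** **1. The plan's own figure.** For 19% against a 40% relative reduction, p2 = 0.6 × 0.19 = 0.114. With two-sided alpha 0.05, power 80%, 1:1 allocation and pooled variance under the null:

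n per arm = [1.960 × √(2 × 0.152 × 0.848) + 0.8416 × √(0.19 × 0.81 + 0.114 × 0.886)]² / 0.076² = (0.9951 + 0.4249)² / 0.005776 ≈ 349.1, rounded up to 350, so 700 in total. The stated sample size is reproduced.

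**2. Inputs for the check.** 1-KM is set to the planning proportions in *Statistics*, 19% (control) and 11% (intervention). The article gives no 180-day mortality, so q is an assumption and is varied. The recorded 5/161 = 3.1% is probably low, because follow-up was incomplete and deaths after an earlier discontinuation would not be listed.

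**3. Formula.** Take constant hazards over the 180 days, λ for readmission and μ for death:

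- λ = −ln(1 − [1-KM]) and μ = −ln(1 − q)
- cumulative incidence (CIF) = λ/(λ + μ) × (1 − exp(−(λ + μ)))

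Control arm, q = 10%: λ = 0.2107, μ = 0.1054, CIF = 0.6667 × (1 − 0.729) = 0.1807.

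| Assumed 180-day mortality, both arms | Control: CIF (1-KM = 19.0%) | Intervention: CIF (1-KM = 11.0%) | Excess of 1-KM, control |
|---|---|---|---|
| 3% | 18.7% | 10.8% | 0.3 points |
| 5% | 18.5% | 10.7% | 0.5 points |
| 10% | 18.1% | 10.5% | 0.9 points |
| 15% | 17.6% | 10.2% | 1.4 points |
| 20% | 17.1% | 9.9% | 1.9 points |

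If 19% and 11% are instead taken as the actual incidences, the plotted 1-KM at 10% mortality would be 20.0% and 11.6%. The gap is of the same size.

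**4. Simulation.** With 400,000 subjects and q = 10%, 1-KM was 19.0% and the Aalen-Johansen estimate 18.1%. With a shared frailty linking death and readmission they were 16.7% and 16.0%. The direction is the same in both.

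**5. Consequence for the comparison.**

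- Equal mortality of 10%: the KM difference is 19.0 − 11.0 = 8.0 points (NNT 1/0.080 = 12.5). The CIF difference is 18.07 − 10.45 = 7.6 points (NNT 1/0.0762 = 13.1). The difference is slightly too large and the NNT too low. The risk ratio is 0.579 on both scales to within 0.001.
- Mortality 10% control, 5% intervention: the CIF difference is 18.07 − 10.73 = 7.3 points, so KM overstates it.
- Mortality 5% control, 15% intervention: the CIF difference is 18.54 − 10.17 = 8.4 points, so KM understates it.

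**The case against.** The strongest case against the point is that nothing of consequence depends on it.

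- The primary outcome is a time to event compared by log-rank test and Cox model. Censoring at death is a standard and valid way to compare cause-specific hazards. This stands in full.
- The article does not promise quoted 180-day risks, risk differences or an NNT; it promises curves. The objective's reference to risk is general wording and does not define an absolute probability as the estimand. This stands, and it limits the point to what the curves show and what readers take from them.
- The article also plans frequencies of readmissions. Counts over all randomised participants would not carry this bias. That helps only in part, since the denominator is not stated.
- The excess is small beside sampling error: 1.96 × √(0.19 × 0.81/350) is about 4.1 points. That is so, but the excess is systematic and avoidable.
- A statistical analysis plan that is not shown may add competing-risk outputs. It may, but the article itself fixes both the censoring rule and the display.

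A reader might also infer that a fatal drug-related event without readmission is credited to the arm as a success. The article does not support this. Censoring takes the person out of the risk set and does not score them as event-free, and mortality is analysed as an outcome of its own. Aalen-Johansen curves would not alter how such a death is classified.

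**Conclusion.** The point holds as a minor one about presentation and interpretation. The plotted 1-KM will exceed the actual probability of drug-related readmission in each arm, by about 0.5 to 1.4 percentage points on 19% if 180-day mortality lies between 5% and 15%. These sizes rest on assumed mortality and constant hazards. The direction within an arm does not depend on either: it follows whenever deaths precede later readmissions.

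A reader might go further and infer that the primary analysis is biased or that 700 is the wrong number. The document does not support that. The test and hazard ratio remain valid on the cause-specific scale, and 700 is reproduced from the stated inputs. Nor can one say that the treatment difference is always exaggerated. That holds with equal mortality, but with unequal mortality the error can go either way, and the article gives no mortality by arm.

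**What to change.** - For drug-related readmission and for unplanned hospital visits, treat death as a competing event. Show Aalen-Johansen cumulative incidence by arm, with values at 30 and 180 days, in place of or beside 1-KM.
- Keep the log-rank test and the Cox model as they are, and label the hazard ratio as cause-specific.
- Report next to it the cause-specific hazard ratio for death before readmission, so that a lower readmission hazard can be read together with any difference in deaths.
- Reword the censoring sentence. Separate death from withdrawn consent, and limit censoring at death to the hazard analyses of readmission and hospital visits. Read literally, the rule would also censor every event in the secondary outcome of time until death.
- Optionally, add the composite of drug-related readmission or death as a sensitivity analysis.

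The cost is a change of wording and a few extra outputs. No new data are needed, since mortality is already collected (Table 2) and time until death is already an outcome. The quoted risks will be slightly lower than those from Kaplan-Meier. The change is best fixed before any unblinded analysis, so that the choice of estimator cannot depend on the results.

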### Data collection and outcomes

All outcome data will be gathered from medical charts with the exception of self-report questionnaires. All collected research data will be coded and kept in locked archives. Before, during and after the trial, all forms and protocols used during the interventions and follow-ups that reveal individual personal data are stored according to the same principle. There will be no identifiable data in the dissemination of the results. In summary, outcomes will be measured at the time of discharge from hospital (baseline) and then after 30 and 180 days, respectively (table 2). The follow-ups on Medication Adherence Report Scale (MARS-5) and EuroQuol five-dimension (EQ-5D) are conducted by phone and preferably in conjunction with the intervention phone calls. Rehabilitation needs require that some enrolled participants are transferred to the geriatric department before leaving the hospital for home. If a participant is relocated to another clinical ward, the actual discharge from hospital will be considered as baseline, with the exception of self-reported adherence and quality of life, which are reported on the original ward. As a consequence, we contact all study participants by phone at 30 and 180 days after their first report regarding MARS-5 and EQ-5D, even if this date differs from the actual date on which they were discharged from hospital.

**Table 2 T2:** Scheduled data collection for primary and secondary outcomes

	Baseline	30 days	180 days

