### Current trial status

The recruitment and enrollment of participants started in September 2018 and there were 20 people enrolled in the trial by the end of that year. From January 2019, additional staff were involved in the recruitment process and the inclusion rate has since increased. The collection of data is currently ongoing, and 161 people had been randomised by November 2019. The intervention, or phone-based follow-ups in the case of controls, had thus far been discontinued for 44 of these individuals. The main reasons were withdrawn consent (n=13), transfers to nursing homes (n=12), repeated unanswered phone calls (n=9) and death (n=5).

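### The protocol conflicts with itself on whether MARS-5 and EQ-5D are still collected after discontinuation, and its status report indicates that in controls they are not

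*Protocol article*

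**What the plan says.** Three sections of the protocol article bear on this.

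- **Data collection and outcomes.** For the two questionnaires, "we contact all study participants by phone at 30 and 180 days after their first report regarding MARS-5 and EQ-5D". The follow-ups "are conducted by phone and preferably in conjunction with the intervention phone calls". Table 2 schedules both instruments at baseline, 30 days and 180 days.
- **Discontinuations and deviations from the protocol.** A participant may withdraw consent or "simply request that remaining phone calls be cancelled". The intervention may also stop for other reasons, "such as a change of living circumstances from home to residential care or repeated unanswered phonecalls". Nothing new is recorded once consent is withdrawn, and death or withdrawn consent is censored in the survival analysis. For everyone else who stops: "In all other cases of discontinued interventions, we collect data regarding hospital readmissions and emergency department visits for the complete 180-day period". The analysis follows an "intention-to-treat principle that includes all randomised participants for the time they were under observation", and "For outcomes other than time to event, we will apply the last observation carried forward in cases of missing data".
- **Current trial status.** At the November 2019 count of 161 randomised, the text reads: "The intervention, or phone-based follow-ups in the case of controls, had thus far been discontinued for 44 of these individuals". Listed as the principal causes are withdrawn consent (13), nursing-home transfer (12), repeated unanswered calls (9) and death (5).

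**The concern.** Medication adherence and quality of life are stated secondary objectives, to be compared in all randomised participants over 180 days. One section commits the trial to asking everyone. Another names only readmissions and emergency department visits as data kept after discontinuation. The status report then describes phone follow-up itself as something that gets discontinued.

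If stopping the service also stops the questionnaires, two secondary outcomes go unmeasured in people who are alive and have not withdrawn. Moving to residential care and not answering the phone are plausibly related to both outcomes, so the missing values are unlikely to resemble the observed ones. The article itself, under Limitations and risk of bias, names MARS-5 and EQ-5D as the outcomes most exposed to bias.

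**Working it through.** **Do the sections conflict?**

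1. The promise of calls at 30 and 180 days covers all participants and makes no exception for discontinuation.
2. The list of data kept after discontinuation omits the questionnaires. That alone does not settle the matter, because the sentence does not say that nothing else is collected.
3. The status report settles it for controls. They receive routine care (Principal study design), and the only phone contact described for them is the MARS-5 and EQ-5D follow-up. Discontinuing a control's phone follow-up therefore means discontinuing the questionnaires.
4. For the intervention arm, the status report says that the intervention was discontinued. The questionnaire calls are only preferably combined with intervention calls, so they could continue alone. That they stop in this arm is an inference.

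**How many people?** The inputs are the counts in Current trial status and the target of 700. The article gives no sample size or power for MARS-5 or EQ-5D, so there is no planned figure to reproduce; 700 serves only as a multiplier.

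- Discontinued for any reason: 44/161 = 27.3%.
- Itemised reasons: 13 + 12 + 9 + 5 = 39, leaving 44 − 39 = 5 with no listed reason. The article claims to list only the main reasons, so this is not an error.
- Nursing-home transfer: 12/161 = 7.5%; 700 × 12/161 ≈ 52.
- Plus unanswered calls: (12 + 9)/161 = 21/161 = 13.0% (exact 95% CI 8.3% to 19.2%); 700 × 21/161 ≈ 91.
- Upper bound, all except withdrawn consent and death: (44 − 13 − 5)/161 = 26/161 = 16.1% (exact 95% CI 10.8% to 22.8%); 700 × 26/161 ≈ 113.

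The three percentages are successively wider counts of one pooled sample.

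**What does the analysis do with them?** Under last observation carried forward, someone who stops before day 30 keeps the baseline score as the day-180 value. That score was given on the original ward, before any move to residential care. Someone who stops between day 30 and day 180 keeps the day-30 score. If p is the share carried forward in an arm and δ is the mean gap between the carried value and the true day-180 value, the error in that arm's mean is p × δ. The error in the comparison is the difference between the arms' p × δ. The documents give neither p by arm nor δ, so no bias can be calculated.

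**The case against.** - **The list need not be exhaustive.** Mortality is a scheduled outcome at 30 and 180 days and is also absent from the sentence on data kept after discontinuation, yet nobody would conclude that deaths go unrecorded. This stands against relying on the omission alone. It does not answer the status report on controls.
- **Stopping is not shown for the intervention arm.** This stands, and the point is worded accordingly.
- **Nobody is dropped from the comparison.** A reader might infer that the adherence and quality-of-life comparisons are confined to people who stayed at home and answered the phone. The documents do not support that: the plan is intention-to-treat with the last value carried forward, and the questionnaires are completed before randomisation. Only the observed later values are confined in this way.
- **Part of the loss is unavoidable.** The 9 had already failed to answer repeated calls, and the 5 with no listed reason may include people who cancelled their calls. This stands, so the clearly avoidable part is the 12 nursing-home transfers.
- **The timing is unknown.** Some of those discontinued may already have given day-30 data. This also stands.
- **Only secondary outcomes are affected.** The primary outcome and hospital visits are explicitly followed for 180 days after discontinuation. This limits the importance of the point but does not remove the conflict.

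**Conclusion.** The conflict is real and should be resolved. The article promises questionnaire calls to all participants, names only hospital events as collected after discontinuation, and reports phone follow-up discontinued in controls, where it can only mean the questionnaires.

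The clearly avoidable part is 7.5% of those randomised, about 52 of 700. With unanswered calls it is 13.0%, and the upper bound is 16.1%. The projections to 700 assume that the November 2019 rate holds. The counts are interim and include people still in follow-up, so the final share could be higher. They also pool the arms and give no timing relative to day 30. Counting discontinued intervention participants as lost to the questionnaires rests on the inference above.

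The consequence is that a baseline or day-30 score, possibly from before a move to residential care, replaces a day-180 value that could have been obtained.

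Two stronger readings are not supported. A reader might infer that the intervention arm loses more people, because it has additional scheduled calls that can go unanswered. The article gives no split by arm, and extra contact could equally improve response. A reader might also want a bias in EQ-5D points, but nothing in the document supplies the quantities needed.

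**What to change.** In Discontinuations and deviations from the protocol, state that discontinuing the intervention does not end outcome collection. The day-30 and day-180 MARS-5 and EQ-5D calls should still be attempted, with the same number of attempts in both arms, for every participant who:

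- is alive,
- has not withdrawn consent, and
- has not asked for calls to be cancelled.

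Say explicitly that this includes people who have moved to residential care. Bring Data collection and outcomes and Current trial status into line, so that stopping the service and stopping questionnaire follow-up are reported separately.

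The cost is a change of wording and modest contact work, since these calls are already promised to everyone. Some non-response will remain. Posted forms for people who do not answer are optional and would add a second mode of administration. With 161 of 700 randomised at the status date, most of the avoidable loss still lay ahead. The change alters no treatment rule and reduces reliance on carried-forward values for two stated secondary objectives.

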### Study population, recruitment and randomisation

The recruitment of study participants started in September 2019 and takes place among emergency admissions to the University Hospital of Umeå. We will continuously recruit participants until we reach the target sample size of 700 randomised individuals. Thus far, recruitment has been limited to one medical ward; however, it is possible to increase the number of wards if the inclusion rate proves insufficient to reach the target sample size during 2022. People who meet the eligibility criteria are given the opportunity to participate in the trial (box 1). Once written consent has been obtained (approval from next of kin in cases of people with major NCD), the participants report self-assessed adherence and quality of life through questionnaires. Following discharge from the ward, the participants are randomly assigned to one of the two study arms through a stratified randomisation procedure (figure 1) based on their results from a shortened 4-item version of the Gottfries’ Cognitive Scale,^31^ a validated tool for proxy rating cognitive impairment.^32 33^ Within each stratum, the participants are further assigned to either of the study arms with an intended ratio of 1:1 through random allocation.

Box 1List of eligibility criteriaInclusion criteria≥75 years.Living at home (ie not in nursing home).Emergency admission.Registered at one of nine specified primary care centres.Exclusion criteriaDo not speak Swedish or unable to communicate.Admitted due to intoxication (drug or alcohol).Scheduled for palliative care.

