**Patient characteristics**			
Age and sex	x		
Cohabitant and home healthcare	x		
Diagnoses	x		
No of medications	x		

Baseline data are collected from the date of hospital discharge. The data for MARS-5 and EQ-5D can be retrieved before the participants are discharged and the date on which questionnaires are completed are considered as baseline regarding these two outcomes.

EQ-5D, EuroQuol five-dimension; MARS-5, Medication Adherence Report Scale.

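### Carrying the last observation forward for MARS-5 and EQ-5D copies day-30 scores, or pre-randomisation ward scores where day 30 is missing, to day 180 and tests them as observed data

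*Protocol article*

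**What the plan says.** The section on discontinuations and deviations sets one rule: "For outcomes other than time to event, we will apply the last observation carried forward in cases of missing data". It names no exception for outcome type, reason for loss or death.

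MARS-5 and EQ-5D are scheduled at baseline, day 30 and day 180 (Table 2). Recruitment "takes place among emergency admissions to the University Hospital of Umeå". The section on data collection takes hospital discharge as baseline "with the exception of self-reported adherence and quality of life, which are reported on the original ward", and the note to Table 2 adds that "the date on which questionnaires are completed are considered as baseline regarding these two outcomes". Randomisation follows discharge from the ward, so these first scores precede it. For follow-up, "we contact all study participants by phone at 30 and 180 days after their first report regarding MARS-5 and EQ-5D".

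Death is dealt with in one sentence: "Any documented death or withdrawn consent is censored in the survival analysis from that point and onwards". Nothing new is recorded after consent is withdrawn. For other discontinuations, "we collect data regarding hospital readmissions and emergency department visits for the complete 180-day period"; questionnaires are not named there. The statistics section offers tests such as chi-square and the independent-sample t-test for secondary outcomes.

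On progress to November 2019, with 161 randomised: "The intervention, or phone-based follow-ups in the case of controls, had thus far been discontinued for 44 of these individuals". The reasons listed are withdrawn consent (13), nursing home (12), unanswered calls (9) and death (5).

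**The concern.** The rule is a fixed choice in the article, so it is not a detail left to an analysis plan. With only three time points there are two values that can be carried to day 180: the day-30 score or the ward score. The ward score was given during an acute illness and before allocation. It cannot reflect the intervention, and it represents day 180 only if nothing changes after discharge.

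Three consequences follow.

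- With equal loss, carried ward scores pull the difference between arms towards zero.
- With unequal loss, any general change between ward and day 180 appears as a difference between arms. Unequal loss is plausible: the intervention arm is called within 7 days and at days 30 and 60 in addition to the questionnaire contacts, while controls have only the questionnaire contacts. Cancelled and unanswered calls are named routes to discontinuation.
- A t-test on the completed data makes no allowance for values having been filled in, so its standard error ignores the imputation.

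Adherence and quality of life are stated secondary objectives. The one supplementary analysis named is per-protocol, among people who received all scheduled interviews, and it does not test the missing-data assumption.

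**Working it through.** The article gives no sample size or missingness figure for the questionnaires, so there is no figure of its own to reproduce on this point. The steps below show what the rule does under stated assumptions.

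**1. Scale of loss (section on current trial status).** Discontinued: 44/161 = 27.3%. Withdrawn consent: 13/161 = 8.1%. Deaths: 5/161 = 3.1%. Reasons not itemised: 44 − 13 − 12 − 9 − 5 = 5. These are discontinuations at any time, not split by arm or by whether a day-30 score exists.

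**2. Dilution with equal loss.** Let m be the share with no day-180 score in both arms, f the part of that share with no day-30 score either, and δ30 and δ180 the true mean differences between arms, assumed the same in those lost. The expected day-180 difference under the rule is

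(1 − m) × δ180 + m × (1 − f) × δ30 + m × f × 0.

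The last term is zero because ward scores are equal in expectation by randomisation. If δ30 = δ180 = δ, this becomes (1 − m × f) × δ. If everyone lost carries the ward score (f = 1), it is (1 − m) × δ.

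Take δ = 4 points on the EQ-VAS (assumed) and m = 0.27 (the discontinuation share, used as a stand-in):

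- f = 0.25: 4 × (1 − 0.27 × 0.25) = 3.73
- f = 0.5: 4 × (1 − 0.27 × 0.5) = 3.46
- f = 1: 4 × (1 − 0.27) = 2.92

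The last figure also results for any f if there is no effect yet at day 30 (δ30 = 0).

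**3. Bias with unequal loss.** Suppose there is no true effect, scores change by c between ward and day 180, and shares pI and pC carry the ward score in the intervention and control arms. The rule alone then produces a difference of c × (pC − pI). With assumed shares of 20% and 35%:

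- c = 0.2 SD: 0.2 × 0.15 = 0.03 SD
- c = 0.5 SD: 0.5 × 0.15 = 0.075 SD

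With 350 per arm, the standard error of a mean difference is √(2/350) = 0.076 SD. These biases are therefore about 0.4 and 1.0 standard errors. The chance of a significant result in the biased direction would be 5.9% and 16.7%, against a nominal 2.5%. Exchanging the shares reverses the sign.

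**4. Deaths and event counts.** The rule covers all outcomes other than time to event, and death is addressed only for the survival analysis. Read literally, the rule therefore reaches the questionnaires of people who died (5/161). The frequencies of readmissions and visits are also outcomes other than time to event. They are collected for the full 180 days except after death or withdrawn consent. No event can follow death, so the counts left incomplete are those of people who withdrew consent (13/161). Carrying such a count forward assumes no further events.

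**The case against.** The best defence is that the rule matters less than it appears to, and much of this stands.

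- *Ward scores.* A reader might infer that ward scores generally stand in for day 180. They do so only where day 30 is missing as well, and the article does not give that split.
- *Amount missing.* A reader might take 27% as the share of questionnaires that will be imputed. It is not. It counts discontinuations at any time, and people who stopped only the intervention may still answer, since all participants are to be contacted at days 30 and 180. Many participants were also still in follow-up, so the final share could be higher. The value 2.9 is thus the unfavourable end of a range.
- *Size of effect.* The dilution formula assumes the full effect in people who stopped early. If their true effect is smaller, the rule dilutes less. Dilution depends on mean differences between arms, so individual scores need not be stable for it to be absent. The bias in step 3 rests on assumed inputs and is small at its lower end.
- *Death.* A reader might infer that the plan sets out to give people who died a living person's quality of life. The article does not say this. It limits analysis to the time under observation, and values after death need not count as missing. That phrase does not say how their questionnaires are analysed, however, so the text needs clarifying.
- *Counts.* A reader might infer that event counts are frozen for everyone who discontinued. The 180-day collection rule excludes that.

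None of this defends carrying a pre-randomisation score forward as a day-180 outcome. The article already advises caution over MARS-5 and EQ-5D, but because of the researchers' dual roles and the lack of blinding, not because of missing data.

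**Conclusion.** The concern holds for the MARS-5 and EQ-5D comparisons and should be fixed. As written, the rule fills day 180 with day-30 scores or with pre-randomisation ward scores, and the tests named would treat these as observed.

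On an assumed 4-point EQ-VAS effect, 27% missing at day 180 in both arms and the same effect in those lost, the expected difference lies between about 3.7 and 2.9. The first figure also assumes that a quarter were lost before day 30 and that the day-30 effect equals the day-180 effect; the second assumes that all were lost before day 30. With unequal loss the bias can go either way. Neither the true missingness nor its split by arm or time can be read from the article.

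The literal reach of the rule to people who died (3.1% so far) and to counts cut short by withdrawn consent (8.1% so far) is a gap in wording to be closed. It is not a stated intention to impute after death. The primary outcome is time to event and lies outside the rule, so a reader should not infer that the main result is at risk.

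**What to change.** 1. Delete the last-observation-carried-forward rule.
2. Analyse MARS-5 and EQ-5D with a mixed model for repeated measures on all observed values, with baseline score, arm, visit, arm by visit and randomisation stratum. Add a sensitivity analysis that varies the missing-data assumption.
3. State that questionnaire scores are not imputed after death, and report survivors' scores alongside mortality.
4. Analyse event counts with observed follow-up time as an offset.
5. State that the day-30 and day-180 questionnaires continue for people who stop only the intervention and still consent. Settle this while data collection is running, because scores not collected cannot be recovered later.

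The cost is analysis wording and a little programming. Estimates may be somewhat less precise than the present rule would suggest.
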